**Fig 2 pone.0330597.g002:**
[figure not shown]
Participant flow and assessment timeline in the Dino Study (CONSORT diagram). The diagram illustrates participant enrollment, exclusion criteria, randomization, and the timing of pretest (T1), the 18-week intervention, and posttest (T2), including daily diary assessments as part of an intensive longitudinal design.

### Power analysis

At the between-person level, an a priori G*Power analysis [27] indicated that 64 participants per group are required to detect a medium effect size (Cohen’s *d* = 0.5), and 26 per group for a large effect size (*d* = 0.8), assuming α = 0.05 and statistical power of 0.80. Previous studies of the IY Dinosaur Child Program have reported effect sizes between 0.70 and 0.81 for improvements in social competence [19], supporting the planned sample size of 120 to allow for potential attrition.

To evaluate intervention effects on intra-individual and dyadic dynamics via daily diaries, simulation-based power calculations were performed. These simulations examined time by condition (intervention vs. control) interactions in multilevel models, with rolling-window correlations nested within participants/families [28]. With 140 time points per child/ family (i.e., 7 days * 20 weeks), statistical power is expected to exceed 80% for detecting small interaction effects (β = 0.005).

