## Materials and methods

### Study design

This protocol, which adheres to the SPIRIT 2013 guidelines (see S1 File), describes the Dino Study (Daily Intervention-based research on Nurturing Opportunities), a two-arm randomized controlled trial (RCT) designed to evaluate the effectiveness of the IY Small Group Dinosaur Child Program in Dutch children aged 4–8 years with perceived elevated or (sub)clinical levels of conduct problems [20,21,24]. A total of 120 children and one primary caregiver per family will be enrolled and randomly assigned to either an intervention group (n = 60) or a waitlist control group (n = 60), using a 1:1 ratio. The study assesses both group-level effects and individual variability in treatment response by analyzing intensive longitudinal data (ILD) from daily diaries to capture children’s moment-to-moment negative affect, externalizing behaviors, and daily parent–child interactions. The intervention group will receive the Dinosaur Child Program in small groups across 18 weekly sessions. The control group will receive care-as-usual and will be offered the intervention after posttest assessment. Pretest (T1) and posttest (T2) assessments will be conducted using standardized questionnaires and a brief child interview, with T2 scheduled 19 weeks after T1. In addition, daily diary data on children’s emotional states, behavior problems, and parent–child interactions will be collected via the m-Path application [26] during a one-week baseline period, the 18-week intervention, and a one-week follow-up (i.e., 20 weeks total). Parent and child will complete the diary jointly each evening (Fig 1). Eligibility criteria include: (a) child age between 4 and 8 years at the start of the study (September 2025), (b) parental indication that the child shows elevated or (sub)clinical levels of conduct problems in daily life (e.g., frequent defiance, aggression, or rule-breaking behavior), (c) daily contact between the child and the participating parent, and (c) sufficient fluency in Dutch. Children are excluded if they have an intellectual disability (IQ < 70) or insufficient Dutch language proficiency.

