#### Hypothesis 1: Group-level behavioral effects.

To assess whether participation in the Dinosaur Child Program leads to greater improvements in children’s emotional, social, behavioral and cognitive functioning, LCS models will be estimated in Mplus for each primary outcome domain: child externalizing behavior, social competence, emotional understanding, and cognitive functioning. Outcomes will be analyzed separately for parent-reported, teacher-reported, and child-assessed measures. LCS models estimate change over time using latent difference scores, thereby distinguishing true change from measurement error. Intervention condition will be tested as a predictor of pre-to-post change examine differential improvements between the intervention and control group. Each latent change score model will estimate the average change over time, interindividual variability in change, and the effect of group assignment on these change scores. Bonferroni-adjusted significance thresholds will be applied to control for multiple comparisons across outcome domains.

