### Trial registration

The protocol of this study is registered at ClinicalTrials.gov with identification number NCT07051642 on July 9^th^, 2025. Protocol version 1, date 09.07.2025. The first participant has not yet been recruited. Additional details about the trial registration are presented Table 1.

**Table 1 pone.0330597.t001:** Overview of measurements.

Data category	Information
Primary registry and trial identifying number	ClinicalTrials.gov
	NCT07051642
Date of registration in primary registry	July, 9th, 2025
Secondary identifying numbers	TSB_RP2172
Contact for public queries	[name] e-mail: [contact]
Contact for scientific queries	[name] e-mail: [contact]
	Tilburg University, Tilburg, The Netherlands
Scientific title	The Dino Study: Rationale and study protocol for a randomized controlled trial evaluating the Incredible Years Dinosaur Program with daily assessments
Countries of recruitment	The Netherlands
Health condition(s) or problem (s) studied	Behavior problems in children, parent-child relations, oppositional behavior, executive functioning, and social and language skills
Intervention(s)	Active comparator: Incredible Years Dinosaur Program
	Control group: Waitlist control condition
Key inclusion and exclusion criteria	Ages eligible for study: child, adult, older adult
	Sexes eligible for study: both
	Accepts healthy volunteers: yes
	Inclusion criteria: Dutch-speaking children aged 4–8 years, at least one Dutch-speaking parent willing and able to participate in the study
	Exclusion criteria: intellectual disability in the child (IQ < 70), child lives primarily in a different household during weekdays, parent or child does not have sufficient Dutch language proficiency
Study type	Interventional
	Allocation: randomized, 1:1 assignment
	Masking: single (outcome assessor)
	Primary purpose: treatment
	Phase: not applicable
Estimated study start date	September 2025
Estimated primary completion date	April 2026
Target sample size	120
Recruitment status	Not yet recruiting
Primary outcome(s)	Change in social competence (parent and teacher reports) Change in externalizing behavior (parent and teacher reports) Change in executive functioning (parent and teacher reports) Change in language and communication skills (parent reports) Change in child-assessed emotion understanding and problem solving
Secondary outcome(s)	Daily dynamic emotional processes (ILD-based)
	Daily behavioral processes within families (Dyadic ILD-based)

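### The sample size is worked out at unadjusted alpha 0.05, but the primary outcomes are tested at Bonferroni thresholds with 60 per arm, and the correction by domain does not match the nine primary measures

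*Protocol article*

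**What the plan says.** All references are to the protocol article.

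- **Power analysis.** "64 participants per group are required to detect a medium effect size" (d = 0.5), and 26 per group for d = 0.8, "assuming α = 0.05 and statistical power of 0.80". The section then cites earlier effects of 0.70 to 0.81 for social competence, "supporting the planned sample size of 120 to allow for potential attrition". It gives no attrition rate.
- **Study design.** Children are assigned 1:1 to "either an intervention group (n = 60) or a waitlist control group (n = 60").
- **Hypothesis 1.** Latent change score models are fitted for each primary domain, listed as "child externalizing behavior, social competence, emotional understanding, and cognitive functioning". Parent, teacher and child measures are analysed separately. "Bonferroni-adjusted significance thresholds will be applied to control for multiple comparisons across outcome domains". No divisor or numeric threshold is given.
- **Outcome measures.** Nine measures carry a primary label: CBCL Externalizing, P-COMP, BRIEF-2 parent, CCC-2-NL, TRF Externalizing, T-COMP, BRIEF-2 teacher, and the two Wally tests (feelings and problem solving). The ECBI sits under the same primary heading as the CBCL, as a complement to it.
- **Trial registration, Table 1.** The primary outcomes include "Change in language and communication skills (parent reports") and child-assessed problem solving. The four-domain list names neither.

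**The concern.** Two stated rules disagree. The sample size assumes alpha 0.05, while the analysis applies a stricter threshold to every primary outcome, so no primary test runs at the alpha that was used for sizing. In addition, 60 per arm is below the article's own 64 for a medium effect before any child is lost, so at that effect size 120 leaves no room for attrition.

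The multiplicity rule has a related problem. Its family is described by domain, but the tests are done by measure and informant. A threshold set by counting domains would be applied to about twice as many tests.

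At stake is how both kinds of result are read. A null result on externalizing behaviour or executive function could be taken as informative when power for a medium effect is near one half. A positive result could be called significant under a threshold whose divisor was never fixed in the article.

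**Working it through.** **Inputs.** Alpha 0.05, power 0.80, d = 0.5 and 0.8, effects 0.70 to 0.81, n = 64 and 26 per group (Power analysis); 60 per arm (Study design); four named domains (Hypothesis 1); nine primary measures (Outcome measures). Assumed here: two-sided tests, which the article does not state but which alone reproduce its figures; attrition of 0 to 20%, because no rate is given; no gain from the pretest; no clustering.

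**Formula.** Two-sample t-test with n per arm: df = 2n − 2, noncentrality = d·√(n/2), power = P(|T| > t at 1 − α/2).

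**Reproducing the article's figures.**
- d = 0.5, n = 64: noncentrality 0.5·√32 = 2.83, power 80.1%.
- d = 0.8, n = 26: noncentrality 0.8·√13 = 2.88, power 80.7%.

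Both sample sizes reproduce exactly. One-sided tests would need only 51 and 21.

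**Power at the planned size and thresholds.** The thresholds are 0.05, 0.05/4 = 0.0125 (four domains) and 0.05/9 = 0.0056 (nine measures). For 60 per arm and d = 0.5 the noncentrality is 0.5·√30 = 2.74, against critical values of 1.98, 2.54 and 2.82.

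| n per arm (attrition) | d | 0.05 | 0.05/4 | 0.05/9 |
|---|---|---|---|---|
| 60 (none) | 0.50 | 77.5% | 58.1% | 46.9% |
| 48 (20%) | 0.50 | 67.9% | 46.5% | 35.4% |
| 60 (none) | 0.70 | 96.7% | 90.1% | 84.1% |
| 54 (10%) | 0.70 | 95.0% | 86.1% | 78.8% |
| 48 (20%) | 0.70 | 92.4% | 80.9% | 72.1% |
| 60 (none) | 0.81 | 99.3% | 97.0% | 94.4% |

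Moving from 64 to 60 at alpha 0.05 costs 80.1 − 77.5 = 2.6 points. The stricter threshold costs far more: 77.5 − 58.1 = 19.4 points at 0.05/4 and 77.5 − 46.9 = 30.6 points at 0.05/9.

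**Attrition margin at d = 0.70.** For 80% power the trial needs 34, 48 and 56 per arm at the three thresholds. The last two allow attrition of 1 − 48/60 = 20% at 0.05/4 and 1 − 56/60 = 6.7% at 0.05/9. At d = 0.5 the requirement is 64, 91 and 107 per arm, all above 60.

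**Smallest effect with 80% power at 60 per arm.** d = 0.52, 0.62 and 0.67.

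**Family-wise error if the divisor is four.** Nine tests at 0.0125 each:
- Bonferroni bound: 9 × 0.0125 = 11.25%.
- Independent tests: 1 − (1 − 0.0125)^9 = 10.7%.

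**The case against.** **The article does not claim 80% power at d = 0.5 with 120 children.** This is correct. It gives 64 and 26 as benchmarks and rests N = 120 on effects of 0.70 to 0.81. At d = 0.70 with 60 per arm, power stays above 80% at either adjusted threshold. A reader might infer that neither the power nor the error control of this trial holds; the documents do not support that. They also do not support limiting the attrition statement to unadjusted alpha, because at 0.05/4 and d = 0.70 the trial tolerates 20% loss. What remains is that the supporting range is cited for one construct.

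**The divisor of four is inferred.** Also correct. Four is the natural reading of a correction across domains where four are listed, but no number is fixed, and an analysis plan not shown might set one. The 10.7% is conditional on that reading. The mismatch between a family defined by domain and tests run by measure and informant is in the article itself.

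**Language and problem solving may fall under cognitive functioning.** Possible: H1 groups cognitive and linguistic competencies together. Their absence from the four-domain list is loose wording and does not show that they were dropped. Likewise, the CBCL composite is already named as the primary indicator, so nine tests is a fairer count than eleven.

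**The planned model uses the pretest.** A gain is plausible. If the analysis adjusts for baseline with an assumed pre-post correlation of 0.6 or 0.7, d = 0.5 acts like 0.5/√(1 − 0.36) = 0.625 or 0.5/√(1 − 0.49) = 0.70. Power at 60 per arm is then 81% or 90% at 0.05/4, and 72% or 84% at 0.05/9. The article assumes no such gain in its sizing, so it cannot be credited unless it is stated.

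**Other families or procedures are defensible.** True. The need is for one declared family that matches the tests.

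**Conclusion.** The point stands in a limited form. The between-person sizing is calculated at an alpha that the primary analysis does not use, and 60 per arm is below the 64 quoted for a medium effect. Under the article's own t-test, power at d = 0.5 is 58% or 47% at the adjusted thresholds before attrition. At d = 0.70 it is 90% or 84%, with an attrition margin of 20% or about 6%. Since the larger effects are cited for social competence only, nothing in the article supports adequate power with an attrition margin for the other primary outcomes.

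Error control is not established, rather than shown to fail: it fails (10.7% if the tests are independent, at most 11.25%) only if the divisor is four.

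The figures assume two-sided tests, no pretest gain and no clustering; the attrition rates are illustrative. Sessions are delivered in groups, but the article gives no intraclass correlation, so no clustering loss is quantified here.

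**What to change.** In the Hypothesis 1 section, list the nine measure-level primary tests as one family, state that the ECBI is supportive, and control the family at 0.05 overall. Holm is suitable because it is never less powerful than Bonferroni. Align the named domains with the primary outcomes in Table 1, so that language and problem solving have an explicit place.

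In the Power analysis section, restate power or the detectable effect for 60 per arm at the adjusted alpha, with an explicit attrition assumption and any assumed gain from the pretest. Limit the statement about allowing for attrition to social competence at d of at least 0.70, with the margin that holds at the adjusted alpha (about 6% at 0.05/9).

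The cost is wording only. No additional children are needed, and the article states that recruitment had not begun, so the family can be fixed before any data exist. The price is that the stated figures become less favourable.

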### Randomization

This single-blinded RCT uses a randomized allocation procedure with a 1:1 allocation ratio to assign participants to either the intervention or waitlist control group. An independent researcher will generate the random allocation sequence using a computer-based random number generator. The personnel responsible for enrolling participants and assigning them to interventions will not have access to the random allocation sequence until after the baseline assessment is completed, at which point parents will be notified of the group assignment.

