**Methods:**

This protocol outlines a randomized controlled trial with a waitlist control condition. A total of 120 children will be randomly assigned (1:1) to the intervention or waitlist group. Participants will be recruited via professional institutions and primary schools in both preventive and clinical contexts. In addition to pre- and post-assessments, Intensive Longitudinal Data (ILD) will be collected to capture daily fluctuations in mood, behavior, and family interactions before, during, and after the intervention. This design enables analysis of group-level effects as well as intra-individual change patterns.

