### Recruitment

Participants will be recruited from primary schools as well as preventive and clinical settings in collaboration with two mental health institutions. Information will be shared via email, school newsletters, posters, and individual consultations. Schools previously engaged in the IY training network will be prioritized. Parents who express interest will complete an online registration form and subsequently participate in a video call with trained research staff, who will confirm eligibility and provide detailed information about the study. During this call, digital informed consent will be obtained from parents or legal guardians. When appropriate, children will accompany this call and be given age-appropriate information and asked to provide verbal or digital assent. Participants will have the opportunity to ask questions and may withdraw from the study at any time without consequence.

Approximately one month prior to the intervention, families will receive a home visit to establish rapport and conduct baseline procedures. In the intervention group, this visit will be conducted by the child’s future group leader; in the control group, by a trained research assistant. During the visit, children will provide oral assent and complete a brief, age-appropriate interview. Parents will complete baseline questionnaires and receive instructions for installing the m-Path app [26]. An overview of participant flow, including enrollment, randomization, and assessment timing, is shown in Fig 2.

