### Intervention

#### Incredible Years Small Group Dinosaur Child Program.

The intervention group will receive the IY Small Group Dinosaur Child Program, a structured, manualized cognitive-behavioral intervention originally developed to support young children (ages 3–8) with conduct problems [20,21,24]. The program is designed to enhance emotional regulation, prosocial behavior, and problem-solving abilities through developmentally appropriate, interactive group-based sessions. Although initially developed for children with externalizing difficulties, it is now widely applied in broader populations, including children with internalizing difficulties such as social-emotional or attentional challenges [33]. In this study, the intervention will target children aged 4–8 years who exhibit elevated levels or (sub)clinical levels of conduct problems.

The program will be delivered in ten small groups, each consisting of 5–6 children. Each group will be facilitated by one certified group leader, using the Dutch translation and adaptation of the original IY protocol. Sessions will be held weekly for 18 weeks, with each session lasting approximately two hours. The curriculum will include storytelling with puppets, video modeling, role-play exercises, group discussions, and cooperative games. These elements are intended to foster emotional awareness, frustration tolerance, interpersonal problem-solving, and socially appropriate behavior. Parents in the intervention group will not receive a parallel parent training during the study period.

All groups will be led by one of six certified IY group leaders. Four of these professionals will be licensed child therapists affiliated with Psychologenpraktijk Timmers or Stichting Kumbaya, and two will be affiliated with Tilburg University. Prior to the start of the trial, all trainers will have completed the official IY certification process, which includes delivery of a full intervention cycle and a successful video-reviewed evaluation of fidelity and delivery quality.

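### Recruitment setting (clinical versus preventive/school) is neither a named stratification factor nor a pre-specified covariate, and the only stated covariate rule depends on baseline significance tests

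*Protocol article*

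**What the plan says.** All places are in the Protocol article.

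- **Recruitment.** The Recruitment section states: "Participants will be recruited from primary schools as well as preventive and clinical settings in collaboration with two mental health institutions". The Abstract says the same, and the Discussion counts delivery in both kinds of setting as a strength.
- **Eligibility.** The Study design section applies the same criteria to every child. The severity criterion is "parental indication that the child shows elevated or (sub)clinical levels of conduct problems in daily life".
- **Allocation.** The Randomization section says that the trial "uses a randomized allocation procedure with a 1:1 allocation ratio to assign participants to either the intervention or waitlist control group", and adds: "An independent researcher will generate the random allocation sequence using a computer-based random number generator". It mentions no strata. It also does not call the sequence simple or unrestricted.
- **Arm sizes and places.** Under Study design, children are "randomly assigned to either an intervention group (n = 60) or a waitlist control group (n = 60), using a 1:1 ratio". The Intervention section says: "The program will be delivered in ten small groups, each consisting of 5–6 children".
- **Adjustment.** Under Preliminary analyses, demographic characteristics, parenting behaviour and child behavioural outcomes are compared between arms at baseline by t-test or Mann–Whitney test. Those that differ significantly become covariates. Setting is not listed.
- **Models and subgroups.** The paragraphs on Hypotheses 1 to 3 do not mention setting. The moderators are child traits (sensitivity, temperament, executive functioning). The subgroup examples are age, gender and baseline severity.

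**The concern.** Children who come through a mental health institution may plausibly differ from children recruited through schools or prevention in severity, in other support received, and in expected change over 19 weeks. The documents give no figure for this, so it is an expectation. If it holds, setting is a prognostic factor, and it should be identifiable from the recruitment route before allocation.

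There are two usual protections for such a factor: balance it by design, or adjust for it by a rule fixed in advance. As described, the plan does neither. Its stated rule makes adjustment depend on a significance test, and setting is not among the variables tested. Such a rule is a weak remedy. It can miss an imbalance large enough to matter, and it leaves the final model unknown until the baseline data are seen. At stake are the precision of the arm comparison and how convincing it looks if the arms differ visibly in clinical share.

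**Working it through.** **1. The plan's own figures.** The Power analysis section gives 64 and 26 per group for d = 0.5 and d = 0.8 (alpha 0.05, power 0.80). The two-sided two-sample t-test solution is 63.77 and 25.52, which round up to 64 and 26, so both figures reproduce. With the planned 60 per arm, power at d = 0.5 is 77.5%.

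**2. Places.** Ten groups of 5 to 6 give 10 × 5 = 50 to 10 × 6 = 60 places. The target of 60 equals the ceiling.

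**3. Chance gap in clinical share, arms fixed at 60/60, no strata.** Let K of the 120 children be clinical. The number X in the intervention arm is hypergeometric (120, K, 60), and the gap is |X − (K − X)|/60. The clinical share is not stated, so a range is assumed.

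| Assumed clinical share | K | P(gap ≥ 10 points) | P(gap ≥ 15 points) |
|---|---|---|---|
| 20% | 24 | 25.4% | 3.9% |
| 30% | 36 | 31.9% | 7.2% |
| 40% | 48 | 35.2% | 9.3% |
| 50% | 60 | 36.1% | 10.0% |

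**4. What a significance test would catch.** If setting were tested, the smallest significant gap at 60 per arm is about 1.96 × √(2p(1 − p)/60).

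- p = 0.2: 1.96 × √(0.32/60) = 1.96 × 0.073 = 14 points.
- p = 0.5: 1.96 × √(0.50/60) = 1.96 × 0.091 = 18 points.

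A 10-point gap would therefore never trigger adjustment in this range.

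**5. Size of the shift.** Shift = gap × difference between settings in the analysed outcome. Assume that this difference is 0.5 to 0.8 SD (not in the documents).

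- 10-point gap: 0.10 × 0.5 = 0.05 SD to 0.10 × 0.8 = 0.08 SD.
- 15-point gap: 0.15 × 0.5 = 0.075 SD to 0.15 × 0.8 = 0.12 SD, which is 15% to 24% of d = 0.5.

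For comparison, the standard error of a standardised difference is about √(2/60) = 0.18 SD.

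**6. Precision to be gained.** Setting would explain about p(1 − p) × (difference)² of the outcome variance.

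- Low end: 0.2 × 0.8 × 0.5² = 0.04, so the standard error falls by 1 − √0.96 = 2%.
- High end: 0.5 × 0.5 × 0.8² = 0.16, so it falls by 1 − √0.84 = 8%.

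The gain is smaller where the baseline score already carries the same information.

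**The case against.** **This is only detail left out of a condensed article.** Block sizes and strata are commonly left to the full protocol, and a figure on participant flow is not shown. This stands for the mechanics of the list: not stating them is no error. It does not cover the covariate rule, which the article states, and which could be improved without any further detail.

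**A reader might infer that the sequence is unrestricted and cannot deliver 60/60.** The text does not support this. A random number generator can equally produce a blocked or fixed-total list, and a 1:1 ratio with 60 per arm fits such a list. Only if simple randomisation were used would Binomial(120, 0.5) apply. It gives exactly 60/60 with probability 7.3%, and more than 60 in the intervention arm with probability 46.4%. Even then the power cost is small: 76.1% at 71/49, against 77.5% at 60/60.

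**A reader might also infer that the trial mixes two populations.** The article describes several recruitment routes under common criteria, with the same severity criterion for all. That severity differs by route is plausible but not shown.

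**Severity is measured directly, and Hypothesis 1 models change.** This stands in part. A baseline difference does not carry over one-for-one into change, so the shifts above need settings to differ in change itself. Baseline severity is also an example subgroup factor in a list left open.

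**Chance imbalance is not bias.** This stands. The 0.18 SD standard error already includes this variation, and the unadjusted test remains valid. The case for acting is precision and credibility.

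**Conclusion.** The point holds as a cheap improvement of minor severity. Recruitment deliberately spans clinical and preventive/school settings. As described, setting enters neither the allocation nor any pre-specified adjustment, and the significance-triggered rule is a poor substitute.

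With 60 per arm and no strata, a gap of 10 or more points in clinical share occurs in about one allocation in four to one in three, and a gap of 15 or more in about 4% to 10%. These figures assume a clinical share of 20% to 50%. The consequence for the estimate further assumes that settings differ by 0.5 to 0.8 SD in the analysed outcome. If they hardly differ, little is lost. Nothing here shows that the comparison is biased in expectation or that the planned arm sizes will be missed.

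**What to change.** 1. **Randomization section.** Stratify the independent researcher's sequence by recruitment setting (clinical versus preventive/school), with the two categories defined beforehand, since the two institutions may serve both preventive and clinical families. Use a restricted list so that the intervention arm stays within 60 places. Fixed totals per stratum guarantee this, but they need the number of children per setting to be known when the list is applied. The Timeline allows that if allocation follows the close of recruitment on October 3, 2025. Small blocks within strata are the alternative, but an unfinished block in each stratum can overshoot slightly: with blocks of 4 the intervention arm could reach 62.
2. **Statistical analysis section.** Include setting as a fixed covariate in the models for Hypotheses 1 to 3, whatever the baseline tests show.
3. **Optional.** Name setting among the exploratory subgroup factors.

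The cost is slightly more administration, one model term, and a small risk of predictable allocations, limited by keeping the list with the independent researcher. No extra data should be needed if the recruitment route is recorded at intake. The Trial registration section says that no participant had been recruited, so the allocation could still be changed at that version. Should allocation since have taken place, the covariate can still be fixed before the outcome data are analysed.
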